## Abstract

There is a strong association between alcohol use disorder (AUD) and intimate partner violence (IPV), both widely prevalent global health issues. However, few interventions target both IPV and AUD, include both partners in the intervention, and are delivered by non-specialist providers in low- and middle-income country (LMIC) settings with scarce mental health resources. This paper describes the protocol for a randomized controlled trial of a combined motivational interviewing (MI) and behavioral couples therapy (BCT) intervention delivered in urban primary care settings in India by nurses with no behavioral health training prior to joining the study. A total of 400 couples will be enrolled and randomized to one of two arms: an intervention arm comprised of 10, hour-long sessions of the MI + BCT intervention, and a control arm receiving enhanced usual care and medical-legal referrals. Data collection will take place at five timepoints: baseline (pre-intervention), three-, six-, nine-, and 12-month follow-ups. Primary quantitative outcomes include the frequency of intimate partner violence over the last 6 months and self-reported quantity and frequency of alcohol use, drinking behaviors, and alcohol-related problems as assessed on the Alcohol Use Disorders Identification Test (AUDIT). Secondary outcomes include number of days with a negative breathalyzer test over a one-week period, communication patterns, and the quality of marital relationship. Qualitative interviews with a sub-sample (n = 40 couples) from the intervention arm will take place immediately post-intervention and at 12 months to explore underlying mechanisms of change. If successful, study results can inform future efforts to develop scalable interventions for IPV and AUD that can be sustained in the Indian public health system through existing PHC staff and infrastructure and be adapted to similar sociocultural settings.

## Introduction

Alcohol use disorder (AUD) and intimate partner violence (IPV) are interconnected issues with significant adverse global public health implications [1]. Globally, an estimated 30% of women report physical or sexual violence by an intimate partner in their lifetime [2]. An increasingly large body of evidence globally supports a causal relationship between AUD and IPV, defined as psychological, physical, and sexual violence, as well as abusive control, by a close partner [1,3,4]. AUD is associated with lowered inhibitions and distorted perception of cues resulting in increased aggression [5–7]. There is growing consensus that AUD in one or both partners is associated with severity and frequency of violence globally [1–3,8,9], including in India [10–16].

In a 2019–2021 national survey among ever-married women in India, 29% reported experiencing physical spousal violence [17], while multi-site studies estimate that up to 52% of Indian women have experienced some form of spousal abuse in their lifetime [18]. Studies in India have found that women with spouses who drink alcohol are more likely to experience violent events [10–16]. Women in India who report IPV victimization can experience poor short- and long-term health outcomes including increased risk for sexually transmitted infections and HIV [19,20], poor maternal health outcomes, [21] and increased suicide risk [20].

Despite strong links between IPV and AUD, there is a dearth of effective and scalable interventions that simultaneously target both AUD and IPV. A 2019 global meta-analysis found few interventions that targeted both AUD and IPV in the United States, Europe, Africa and India, [22] and among those, none were successful in changing both target behaviors, [22–27] highlighting a large scientific gap. Furthermore, interventions that have been successful at reducing either alcohol use or IPV are delivered by mental health professionals, limiting scalability [22]. Interventions in the US [23–25] have employed cognitive behavioral therapy (CBT) techniques using group and individual sessions delivered by trained masters-level therapists [23,25] to strengthen problem-solving and communication skills among incarcerated men. These studies found a significant reduction in self-reported days of alcohol use, [23] and participants were less likely to report engaging in aggressive behaviors after drinking episodes [25] but found no significant difference in reported frequency of physical IPV. Other studies in the US added substance use treatment in addition to IPV treatment as usual but did not find statistically significant changes in outcomes [28,29].

Evidence from global systematic reviews of AUD and IPV intervention studies suggest two major gaps. First, most often, only the male partner was engaged in the intervention [22–27,30]. Despite ongoing IPV, many women, particularly from LMIC settings, cannot or may not want to leave their partners [31]. In such cases, working with couples on communication and conflict negotiation has been effective at reducing violence [32–38], suggesting that couples therapy may be more effective than individual treatment. The second gap is that most studies failed to integrate treatment for both AUD and IPV [30]. Behavioral couples therapy (BCT), which is based on principles of CBT and improvement of interpersonal relationships, can be effective at reducing IPV [27,39]. When BCT is offered when the husband has AUD, it is important to first deliver a program to reduce his alcohol use [27,39,40]. Given the pervasiveness of IPV and its association with AUD, there is a strong need for evidence-based interventions that overcome these gaps, are culturally appropriate, and are tailored to the population of interest.

Our study team conducted a pilot intervention in 2017 in Bengaluru, India [36] in which BCT was combined with contingency management (an empirically supported, behavioral substance use treatment) to reduce AUD and IPV among 60 couples, including both partners and combining treatments for both AUD and IPV. Results showed that the intervention significantly reduced men’s alcohol use (measured by daily breathalyzer testing) and IPV (based on the Indian Family Violence and Control Scale (IFVCS) [41] at one- and four-month follow-up periods. Participant couples reported the intervention did not lead to an increase in violence, an important concern when enrolling couples in IPV interventions. The BCT component was described as a strategy to improve communication and relationships, which improved acceptability, recruitment, and retention of vulnerable couples.

The current RCT is based on the results of this pilot study, replacing the contingency management component with motivational interviewing (MI), a robust intervention with substantial evidence in reducing AUD in multiple populations globally [42], including India [43]. This increases the scalability of the intervention by avoiding concerns of ongoing monetary incentives as part of contingency management for alcohol use. To ensure the intervention has the highest likelihood of success and eventual scale-up, we trained nurses to deliver MI and BCT. Several studies have shown that nurse-led MI can successfully reduce alcohol use [43–49] and improve multiple other health outcomes [50–55]. In India, MI has been used widely [56,57], including by non-mental-health professionals to reduce alcohol use [49,58]. These findings demonstrate that in primary care settings, where there is a shortage of mental health professionals, training nurses in MI is feasible and effective at reducing AUD. Our study will thus address gaps in the current literature by using trained nurse-counselors to deliver MI and BCT to reduce AUD and IPV.

### Study objective

This study builds on the prior evidence base and existing infrastructure at primary health clinics in south India by conducting a randomized controlled trial (N= 400 couples) to study the efficacy of MI and BCT in reducing IPV behaviors and AUD among the men. The intervention is delivered by study nurses in communities that are part of the catchment areas of local government-run primary health centers (PHCs) providing services for underserved populations. We will also assess secondary outcomes. Other key measures will be assessed utilizing mixed methods to explore theorized mechanisms of change influencing intervention efficacy. If successful, our study will provide evidence for an intervention for IPV and AUD that can be adapted and delivered by non-specialists in primary care settings in South Asia and other resource-constrained settings with similar cultural norms (see Fig 1).

**Fig 1 pone.0335332.g001:**
[figure not shown]
SPIRIT schedule of enrollment, intervention, and assessment.

### Theoretical framework

The intervention, named “Harmony”, is guided by an integration of Social Cognitive Theory (SCT) [59], MI, and findings from our pilot study [36] (see Fig 2). MI is a “client–centered, directive method for enhancing intrinsic motivation to change by exploring and resolving ambivalence” [60] and is a well-established behavioral intervention strategy to reduce AUD in multiple global settings, including India [42,41,47,48,58]. Because of its tailored nature, MI is an effective strategy to address behavior change to reduce alcohol use while encouraging development of self-efficacy and behavioral skills and is compatible with the SCT framework [60].

**Fig 2 pone.0335332.g002:**
[figure not shown]
Conceptual model to reduce incidence of intimate partner violence via reduction of alcohol use and improvement of relational dynamics based on Social Cognitive Theory, Motivational Interviewing, and empirical data from pilot studies. Hypothesized moderators are listed in italics.

SCT is a strong fit for this intervention because of its emphasis on interpersonal interactions and environmental influences on behaviors, as well as on specific strategies that promote behavior change, all important to reduce barriers and promote facilitators of change. Women often have few options to leave their marriage [35], are subject to the broader norms of their family and society, and often express commitment to staying with their husbands despite ongoing violence [61]. SCT allows us to incorporate these factors at the individual, couple, and environmental levels.

SCT is especially relevant to alcohol reduction efforts as self-regulatory capacity and self-efficacy – central tenets of both MI and SCT – are salient to reducing alcohol use among participants with AUD [59,62]. Self-efficacy, which refers to a person’s confidence in their ability to succeed at a specific task, is a key element in motivation to change. Self-efficacy changes because of learning skills, having formative experiences, and receiving feedback. BCT is rooted in social learning theory and focuses on improving communication, trust, and conflict negotiation skills to enhance the relationship between partners [40]. The key drivers of alcohol use and perpetration of IPV that we have included in the model are antecedents or precipitants that are proximally associated with IPV perpetration and are malleable to a brief psychosocial intervention. While we do not expect that the intervention will impact gender norms or impulsivity, these factors may moderate the intervention effects and will be assessed at baseline. Proximal antecedents of alcohol use and IPV perpetration include contextual factors linked to alcohol use, situational factors linked to violence, cognitive variables (motivation, self-efficacy), affect (anxiety), stress, and behavioral measures such as relationship, communication, coping strategies, and anger control [63–66]. See Fig 2 for a detailed conceptual model.

The two-step intervention strategy proposed is in alignment with the recommendations by O’Farrell and colleagues [40] that BCT be coupled with an intervention directed at reducing harmful drinking. This strategy may create short-term behavior change and increase the likelihood of success of BCT in enhancing the relationship via skills training. MI is intended to provide the requisite reduction in alcohol use to enable the couple to participate in and benefit from the BCT sessions. MI’s client-centered approach trains counselors to express empathy and to adjust to, rather than confront, the discord expressed by people with AUD. MI strategies also help clients discover discrepancies between their goals and their behaviors while enhancing self-efficacy. This approach is consistent with skill-building strategies which are cornerstones of SCT-based interventions, including BCT.

Our pilot study showed that the reduction in violence was likely attributable to reductions in the husband’s use of controlling behaviors towards their female partner, which in turn may have resulted from improved communication skills combined with greater self- and emotion regulation due to reductions in drinking [36]. These results support the use of our integrated SCT-MI conceptual model for improving motivation to reduce harmful drinking, which can lead to improved self-regulatory capacity, followed by skills training and self-efficacy, ultimately promoting healthy couples’ interactional behavior and reducing IPV.

## Materials & methods

The trial has been registered with clinicaltrials.gov (*Trial registration number: NCT05893277)* and with the Clinical Trials Registry – India *(CTRI registration number: CTRI/2022/09/045513)*.

### Study design

The study design (Fig 3) is a mixed methods randomized controlled trial (RCT) of the combined MI and BCT Harmony intervention. Couples will be randomized 1:1 to the control group (n = 200 couples) and the intervention group (n = 200 couples). The dyadic intervention condition consists of 10, hour-long sessions and involves spouses in 3 individual and 7 joint sessions over a five-month period. The control condition consists of enhanced usual care, which includes safety assessments and referrals for IPV resources for the women and brief psychoeducation for AUD for the men. Assessments will be conducted at baseline, 3-, 6-, 9-, and 12-month follow-up. A subset of couples in the intervention arm (n = 40) will be randomly selected to partake in the post-intervention qualitative in-depth interviews (IDIs).

**Fig 3 pone.0335332.g003:**
[figure not shown]
Study design and flow.

### Study setting

The study is conducted in regions served by the government-run urban primary health centers (PHCs) in Bengaluru, India. The Bengaluru metropolis includes several PHCs, and each center serves as a nodal point for delivery of health services to primarily low-income populations in low-resource settings, ranging from 50,000 to 75,000 people per catchment area. The PHCs provide comprehensive primary care, basic emergency care, referrals, basic laboratory testing, pharmacy services, antenatal care, family planning, and immunization services. They also serve as the focal point for outreach work and other public health interventions in the catchment area. Each PHC includes several healthcare workers, including community health workers called Accredited Social Health Activists (ASHAs). Our study will engage eight to nine PHCs and several community-based organizations that operate within the catchment areas of these PHCs for recruitment.

### Eligibility criteria

#### Inclusion criteria.

For all participants, eligibility criteria include: i) married with both spouses aged ≥18 years; ii) living within the catchment area of the PHC; iii) Kannada-speaking; iv) woman reporting physical or sexual IPV in the past 12 months (per adapted version of the International Violence against Women Survey [67] – IVAWS); and v) the husband with AUD (AUDIT-C ≥ 4). [68]

#### Exclusion criteria.

Exclusion criteria include: i) husband has severe alcohol dependence (Severity of Alcohol Dependence Questionnaire, [69] SADQ ≥ 31) or is at risk of severe withdrawal symptoms based on Clinical Institute Withdrawal Assessment for Alcohol Scale–Revised [70] (CIWA-AR); ii) significant medical problems that will make the couple unable to participate in the intervention sessions; iii) cognitive problems (Short-Blessed Cognitive Test [71] score ≤7); iv) past year history of IPV severe enough to result in hospitalization; or v) wife is positive for AUD (AUDIT-C ≥ 4) at screening [68].

### Sample size determination

Sample size was determined based on the power necessary to detect a meaningful intervention effect at 12 months in the continuous primary outcomes. Based on our pilot results, [36] we expect the intervention group to have a 4-5 point lower mean IFVCS score compared to the control group at the end of the study (SD = 14). With alpha = 0.05, power = 80%, this requires an effective sample size of n = 320. Allowing for 20% attrition, the initial sample size necessary is 400 couples. This anticipated effect translates into a standardized minimum detectable effect size of d = 0.31, a small effect according to Cohen. [71] Since we will treat the AUDIT as continuous as well, we are similarly powered for a significant minimum detectable effect size of 0.31 standard deviations difference between the two groups on this second primary outcome. This is within our expectations based on a meta-analysis [72] that found a standardized mean difference of 0.29–0.38 with brief one-session interventions or usual care, respectively.

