#### Control arm.

Our prior work in India has shown a lack of availability of care for AUD and/or IPV in PHCs, as well as lack of adherence to existing protocols. [76,77] To meet ethical guidelines, the control arm participants receive a single session of enhanced usual care, consisting of (1) validation and safety planning for the wife; (2) referrals to provide medical-legal and shelter support; and (3) a brief educational intervention to the husband on alcohol use, based on the World Health Organization’s manual for managing AUD in primary care settings, [74] and a referral to tertiary care mental health (NIMHANS) and addictions treatment center. These will be carried out within two months of the baseline assessment by a trained nurse practitioner who is not involved in delivering the intervention.

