### Data analysis

#### Quantitative.

We will perform intention-to-treat (ITT) analyses to compare the treatment and control groups on the two primary outcomes: 1) mean overall AUDIT score as the measure of alcohol use; and 2) mean overall IFVCS score as the measure of IPV. We hypothesize that the treatment group will show a lower mean AUDIT score and a lower mean IFVCS score than the control group participants at 12-month follow-up. We will analyze this via a linear regression model for each outcome, in which we will control for the baseline outcome score and any relevant covariates for which the treatment groups might differ at baseline, despite randomization. A multilevel version of the models will be used for the longitudinal analyses, with repeated measures nested within participants and a random intercept for participants. The treatment arm*wave interaction will serve as the test of the intervention effect. Since each of these outcomes will only be collected from one of the spouses (alcohol use from the male and IPV from the female),combining/controlling for multiple reports within the couple is not necessary. If despite our extensive, proven-effective retention efforts, there is a substantial amount of missing data, we will use multiple imputations, assuming data are missing at random, including socio-demographic and other variables as auxiliary variables as appropriate, to perform sensitivity analyses of the original results [103].

Secondary analyses will consist of similar ITT linear regressions as for IFVCS above for the secondary outcomes of mean CPQ and breathalyzer scores. We hypothesize that post-intervention, the treatment group will show more positive and less negative communication patterns than the control group. We also expect that intervention participants will have lower post-intervention breathalyzer scores, on average, than the control group, reflecting reductions in frequency and quantity of alcohol use. Like the primary outcomes, the breathalyzer data is only available from one spouse, but CPQ data will be collected from both spouses. CPQ subscale scores will be constructed based on each spouse’s report separately, and agreement assessed via intraclass correlations. The treatment effect will be explored using husband and wife reports as the outcome variable in separate models to allow a differential effect of the treatment on mean CPQ subscale scores as reported by each partner in the couple [104].

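### The 80% power holds from about 4.4 IFVCS points, not across the expected 4 to 5, and the full 0.05 is spent on each of two primaries

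*Protocol article*

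**What the plan says.** Under Sample size determination, the protocol article bases the calculation on IFVCS: "we expect the intervention group to have a 4-5 point lower mean IFVCS score compared to the control group" at the end of the study, with SD 14. It continues: "With alpha = 0.05, power = 80%, this requires an effective sample size of n = 320". Allowing for 20% attrition, this becomes 400 couples. The next sentence reads: "This anticipated effect translates into a standardized minimum detectable effect size of d = 0.31".

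For AUDIT, the trial is said to be "similarly powered for a significant minimum detectable effect size of 0.31 standard deviations difference between the two groups on this second primary outcome". This is described as consistent with a meta-analysis that found a "standardized mean difference of 0.29–0.38 with brief one-session interventions or usual care, respectively".

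Under Control arm, control couples receive one session of enhanced usual care, which includes "a brief educational intervention to the husband on alcohol use" and a referral.

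Under Data analysis (Quantitative), the plan is to "compare the treatment and control groups on the two primary outcomes", with a separate linear regression for each at 12 months, adjusted for the baseline score. The hypothesis names a lower mean on both outcomes.

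**The concern.** A range of expected effects cannot share one required sample size. The text attaches 320 couples and 80% power to 4 to 5 points and then equates that range with d = 0.31. At SD 14 the range is d = 0.286 to 0.357, so its lower end lies below the detectable effect. The same holds for AUDIT: 0.31 falls inside 0.29 to 0.38, but 0.29 is below what the trial detects with 80% power.

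The second issue is what the 80% refers to. It is the power of each outcome judged alone at 0.05. The stated objective is to reduce both IPV and AUD, so a reader will ask about the chance of success for the trial. If either outcome suffices, the overall false-positive rate is nearly doubled. If both must succeed, the chance of success is below 80% at the planned effects, before any gain from adjustment.

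**Working it through.** **Inputs.** From Sample size determination: alpha 0.05, power 80%, SD 14, 4 to 5 points, 320 evaluable couples, 20% attrition, AUDIT range 0.29 to 0.38. From Study design: 1:1 allocation, hence 160 evaluable per arm. The article does not state sidedness. Two-sided is inferred, because a one-sided 0.05 test at d = 0.31 would need only 258.

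**Reproducing the plan's figure.** Normal approximation: detectable d = (1.960 + 0.842) × √(2/160) = 0.313, and 0.313 × 14 = 4.4 points. The noncentral t gives 0.314, also 4.4 points. Attrition: 320 / 0.80 = 400. In reverse, d = 0.31 needs 164 per arm, or 328, within 3% of 320. The stated size reproduces.

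**Power over the plan's own ranges.** Power ≈ Φ(d × √(160/2) − 1.960), checked with the noncentral t:

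| Effect | d | Normal | Noncentral t |
|---|---|---|---|
| IFVCS 4 points | 4/14 = 0.286 | 72.4% | 72.2% |
| IFVCS 4.5 points | 0.321 | 82.0% | 81.8% |
| IFVCS 5 points | 0.357 | 89.2% | 89.0% |
| AUDIT, lower end | 0.29 | 73.7% | 73.4% |
| AUDIT, upper end | 0.38 | 92.5% | 92.3% |

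Example at 4 points: 0.2857 × 8.944 − 1.960 = 0.596, and Φ(0.596) = 0.724.

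**Effect of baseline adjustment.** With baseline to 12-month correlation r, the residual SD is multiplied by √(1 − r²). Power returns to 80% when r = √(1 − (d / detectable d)²). With the t-based 0.314, this is √(1 − (0.2857/0.3142)²) = 0.42 at 4 points and √(1 − (0.29/0.3142)²) = 0.385 at 0.29. The normal approximation gives 0.41 and 0.38. The article gives no r. Over an assumed r of 0.2 to 0.6, power at 4 points runs from 74% to 89%.

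**Two primaries at 0.05 each.**
- Either suffices: if neither effect exists, familywise error is 1 − 0.95² = 9.75% for independent tests, and 9.1% if the test statistics correlate at 0.5.
- Both needed: at d = 0.314 on each, joint power is 0.80² = 64% if independent, and 69% at correlation 0.5 (bivariate normal). Both are unadjusted. With an assumed baseline correlation of 0.4 or 0.5 on both outcomes, and independence between them, joint power is about 75% or 81%.
- Tested at 0.025: power at d = 0.31 is about 70% and detectable d is 0.346, or 0.346 × 14 = 4.8 points. Under Hochberg, an outcome can also be declared at 0.05 when the other is significant at 0.05. If both effects are 0.31 and independent, power per outcome is therefore 0.699 + (0.789 − 0.699) × 0.789 = 77%.

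**The case against.** The strongest reply is that the arithmetic is right. The article names the effect its 80% belongs to, d = 0.31; 4.4 points lies inside 4 to 5, and power at the midpoint is 82%. It never explicitly claims 80% at 4 points or at 0.29. That stands. What remains is that the text says the expected range requires 320 couples, which is untrue of its lower end.

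Second, an unadjusted sample size is ordinary conservative practice, and the planned regression adjusts for baseline. That also stands: a correlation of about 0.41 to 0.42 would restore 80% at 4 points. But the sample size section neither claims this gain nor states a correlation, so it mitigates the gap without answering it. The 64% to 69% joint power carries the same caveat.

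Third, a reader might infer that 0.29 is the AUDIT benchmark that applies to this trial. The documents do not support that firmly. What the meta-analysis counted as a one-session intervention is not visible, and the control has features of both comparators: it is a form of usual care, delivered in one session with brief alcohol education. It resembles the lower comparator in part.

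Fourth, a multiplicity rule may sit in a statistical analysis plan that is not shown, so its absence from the article is no finding. If both outcomes must succeed, 0.05 each is correct and the familywise figure does not apply. What stands is that the printed power fits only the reading in which each outcome is judged alone.

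A reader might also discount the 4 to 5 points because the pilot reported results "at one- and four-month follow-up periods" and used a different alcohol component. The article discloses both facts and does not show the pilot estimates, so no error is demonstrated.

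**Conclusion.** Wrong as written, and minor. The 320 couples give 80% power from about 4.4 points (d = 0.314) upward. Unadjusted power is 72% at the lower end of the IFVCS range and 73% at the lower end of the AUDIT range, shortfalls of 8 and 7 percentage points. The 80% is also a per-outcome figure at the full 0.05. Depending on the success rule, it goes with a familywise error of 9.1% to 9.75% or an unadjusted joint power of 64% to 69% at the detectable effect.

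These figures assume two-sided tests, 160 evaluable per arm, SD 14 and no baseline adjustment. The two-outcome figures assume a correlation between outcomes of 0 to 0.5. They do not show that the trial is underpowered under its planned model: with a moderate baseline correlation it may reach 80% throughout both ranges.

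**What to change.** Restate the power in Sample size determination:

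- 80% power at two-sided 0.05 applies to differences of about 4.4 points (d = 0.31) or more. Before baseline adjustment it is 72% at 4 points and 73% at a standardized difference of 0.29.
- If baseline adjustment is relied on, state the assumed correlation. About 0.41 to 0.42 restores 80% at 4 points, and about 0.38 to 0.39 at 0.29.
- State one success rule, or cite it if the analysis plan already fixes it. If either outcome suffices, test the two with Hochberg and give the power under it; testing at 0.025 gives about 70% at d = 0.31, with detectable d 0.346. If both are needed, keep 0.05 for each and state the joint power, marked as before baseline adjustment.

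The cost is less favourable printed figures and a sentence on the success rule. Under Hochberg, a lone p-value between 0.025 and 0.05 would no longer count. No extra couples are needed. With recruitment expected to run to September 2026 (Trial status), the change can be made before the final outcome analysis.
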